### 2.8. Objectives

The primary objective is to develop an HRQoL measurement strategy for sarcoma patients, indicating which issues can be included for all sarcoma patients (sarcoma-generic) and which issues should be evaluated in certain subgroups (e.g., based on treatment or sarcoma location) only. This is the first step towards the implementation of sarcoma specific PROs in future clinical trials. Secondary endpoints are: (1)to develop an exhaustive list of all HRQoL issues relevant to sarcoma patients (irrespective of their sarcoma subtype, treatment, time since diagnosis and age, and including generic/specific issues), (2) to determine the proportion of patients in each subgroup (according to tumor localization, type of sarcoma, disease stage and treatment) rating each item and the items from the EORTC QLQ C30 as relevant (i.e., rating 2–4 on Likert scale indicates relevance), (3) to determine the proportion of respondents with head neck or uterine localization rating each site-specific item of the H&N43 or EN24 questionnaire as relevant (i.e., rating 2–4 on Likert scale indicates relevance), (4) to determine the proportion of subgroups rating each item as relevant (i.e., half subgroups rating an item as relevant indicates a sarcoma-generic issue), and (5) to determine subgroup-specific (according to localization, type of treatment, subtype and disease stage) issues using a comparative approach (issues cited at least 1.5 times more indicates subgroup-specificity).

### 2.9. Sample Size Calculation

Part A: No formal sample size calculation can be made for the interviews. Data collection continues until saturation is reached, which is usually after 12 patients in phenomenological research [49]. Saturation occurs when adding more participants to the study (or, in this case, subgroup) does not result in additional perspectives or information. A stratification matrix (Table 1) will be used that ensures that at least 12 patients per location and 10 per treatment will be interviewed, considering the incidence of sarcoma location and treatment. In total, 154 patients will be recruited. Although some locations will be overrepresented in this sample compared to the population-based incidence numbers, this proportion was chosen to make sure that enough patients are enrolled per group to be able to conduct subgroup analyses.

Part B: Although the EORTC guidelines for development state that no more than 10 patients should be included in this part, the heterogeneity of the sarcoma population requires greater numbers for adequate subanalyses. Again, at least 10 patients per location and 10 per treatment will be recruited (Table 1), leading to a total of 475 patients.

Healthcare professionals: According to the EORTC module development guidelines, at least 5 HCPs should be included; therefore, 5 HCPs will be interviewed for each location (i.e., 6 in total), which means 30 HCPs in total. This applies to both parts A and B.

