Additional analyses will be performed per subgroup for location, treatment(s) received (surgery; chemotherapy/targeted therapy; radiotherapy; no treatment), type of sarcoma (soft tissue vs. bone sarcoma), and disease stage (localized vs. metastatic). An issue needs to be endorsed by at least 30% of the patients in a subgroup, and the mean score needs to be 1.5 or higher to be included as an issue in a subgroup. Then the prevalence of each issue between the aforementioned subgroups (according to location, type of treatment, subtype and disease stage and combinations of these factors) will be compared to decide whether an issue is subgroup-specific. Issues that are cited by at least 1.5 times as many respondents in group A compared to group B (a ratio of 3:2) may be considered as subgroup-specific.

For head and neck, and uterine sarcoma patients, the scores on the H&N43 and EN24 will be analyzed. We will assess the prevalence (percentage of the subjects who score higher than 2 is >30% and a mean score of 1.5 or higher) of each site-specific item. When at least 80% of the items are prevalent, using the site-specific module for those sarcoma locations will be recommended.

All the collected information will help to advise researchers as to which factors need to be taken into account when creating an item list for a specific study focusing on subgroups of sarcoma patients.

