**Total**							
Per location							154
Per treatment							
SU only:							34
SU + RT:							26
SU + RT + ST:							14
Surgery total:							74
RT total:	42	20	32	20	20	20	40
ST only:							60
ST total:							74
Local:							10
Per subtype							
Bone:							54
Soft tissue:							100

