**Phase 1b**							
*Localized*							
Bone							
SU	20	4	5	- ^a^	-	-	
SU + RT	20	8	-				
SU(+RT) + ST	20	8	-				235
Soft tissue							
SU	10	-	4	12	24	20	
SU + RT	40	-	4	8	16	-	
SU(+RT) + ST	-	-	12	-	-	-	
*Metastatic/local relapse*							
Bone							
Local treatment (+ST)	20	4	4	- ^a^	-	-	
ST	30	16	16		-	-	240
Soft tissue							
Local treatment (+ST)	10	-	-	-	-	-	
ST	30	-	16	16	32	16	
BSC	10	-	4	4	8	4	30

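### Table 1, Phase 1a: the printed cells add to 140, while the text and the table's own margins say 154; the missing 14 places are all soft-tissue head-and-neck patients on systemic therapy

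*Protocol article*

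**What the plan says.** Section 2.9 of the protocol article gives the Part A size: "In total, 154 patients will be recruited". It makes the stratification matrix the means of securing minimum numbers: "A stratification matrix (Table 1) will be used that ensures that at least 12 patients per location and 10 per treatment will be interviewed". The abstract also gives 154.

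The margins of the Phase 1a block of Table 1 agree with that total:

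- The location totals stand on the radiotherapy line: "RT total: 42 20 32 20 20 20 40". The first six figures are the locations, with head and neck third at 32, and they add to 154. The last figure is the radiotherapy total.
- By stage, the margins are 74 localized and 80 metastatic or relapsed.
- By treatment, they are SU only 34, SU + RT 26, SU + RT + ST 14, ST only 60, local 10 and best supportive care (BSC) 10.
- By subtype, they are bone 54 and "Soft tissue: 100".

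Section 2.5 gives the matrix a working role: the study coordinator stratifies by it and tells local collaborators which patients can be invited.

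**The concern.** The body of the Phase 1a block does not support its own margins. Two entries that Phase 1b contains are absent from Phase 1a. One is the localized soft-tissue row for surgery (with or without radiotherapy) plus systemic therapy. The other is the head-and-neck number in the metastatic soft-tissue systemic-therapy row. In Phase 1b that second row reads "ST 30 - 16 16 32 16", with head and neck third at 16.

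Anyone who fills the matrix cell by cell would assign no Part A interview place to soft-tissue head-and-neck patients treated with surgery plus systemic therapy, or with systemic therapy for metastatic or relapsed disease. Part A feeds the issue list that Section 2.8 wants to be exhaustive, and location and treatment are two of the factors that decide whether an issue is subgroup-specific. A gap where those two factors cross is therefore in an awkward place.

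**Working it through.** **Inputs.** All are from Table 1, Phase 1a. Columns run in the order extremities, axial, head and neck, thoracic, retroperitoneal/intra-abdominal, pelvic organs. Dashes and blanks count as 0.

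**Rows as printed.**

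| Row | Cells | Sum |
|---|---|---|
| Localized bone, SU | 4+2+2 | 8 |
| Localized bone, SU + RT | 4+4 | 8 |
| Localized bone, SU(+RT) + ST | 4+4 | 8 |
| Localized soft tissue, SU | 2+2+6+6+10 | 26 |
| Localized soft tissue, SU + RT | 8+2+4+4 | 18 |
| Metastatic bone, local | 4+2+2 | 8 |
| Metastatic bone, ST | 6+8+8 | 22 |
| Metastatic soft tissue, local | 2 | 2 |
| Metastatic soft tissue, ST | 6+8+8+8 | 30 |
| BSC | 2+2+2+2+2 | 10 |

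Localized: 8+8+8+26+18 = 68. Metastatic including BSC: 8+22+2+30+10 = 72. Total: 68+72 = **140**.

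**Cells against margins.** BSC counts as soft tissue, which is what the printed margin of 100 requires.

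| Margin | Cells | Stated | Gap |
|---|---|---|---|
| Total | 140 | 154 | 14 |
| Localized | 68 | 74 | 6 |
| Metastatic/relapse | 72 | 80 | 8 |
| Head and neck | 2+2+2+2+8+2 = 18 | 32 | 14 |
| Other five locations | 42, 20, 20, 20, 20 | 42, 20, 20, 20, 20 | 0 |
| SU only | 8+26 = 34 | 34 | 0 |
| SU + RT | 8+18 = 26 | 26 | 0 |
| SU + RT + ST | 8 | 14 | 6 |
| ST only | 22+30 = 52 | 60 | 8 |
| Local | 8+2 = 10 | 10 | 0 |
| BSC | 10 | 10 | 0 |
| Surgery total | 34+26+8 = 68 | 74 | 6 |
| RT total | 26+8 = 34 | 40 | 6 |
| ST total | 52+8 = 60 | 74 | 14 |
| Bone | 8+8+8+8+22 = 54 | 54 | 0 |
| Soft tissue | 26+18+2+30+10 = 86 | 100 | 14 |

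**Locating the gap.** Only the head-and-neck column is short, and bone is complete, so all 14 places are soft-tissue head and neck. The localized and SU + RT + ST margins are each short by 6. The metastatic and ST-only margins are each short by 8. The absent entries are therefore 6 (localized soft tissue, SU(+RT) + ST) and 8 (metastatic soft tissue, ST).

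**Check after restoring them.** Total 140+6+8 = 154; localized 68+6 = 74; metastatic 72+8 = 80; head and neck 18+14 = 32; SU + RT + ST 8+6 = 14; ST only 52+8 = 60; surgery total 68+6 = 74; RT total 34+6 = 40; ST total 60+14 = 74; soft tissue 86+14 = 100. Every margin is reproduced.

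**Phase 1b as a control.** Columns: 210+40+65+40+80+40 = 475, as stated. Localized 29+28+28+70+68+12 = 235 and metastatic 28+62+10+110+30 = 240, also as stated. The treatment and subtype margins agree as well. The two Phase 1b counterparts, 12 and 16, are exactly twice 6 and 8. Of the six head-and-neck cells printed with numbers in Phase 1a, five are also doubled in Phase 1b (the exception is bone SU, 2 to 5).

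**Effect on the stratum.** Soft-tissue head-and-neck places as printed: SU 2 + SU + RT 2 + BSC 2 = 6. As the margins imply: 6+14 = 20.

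**The case against.** A reader might infer that Part A will deliver only 140 patients. The document does not support that. The abstract, Section 2.9 and the Phase 1a margins all say 154, and the margins are mutually consistent and fix the two absent entries. Section 2.9 also says that interviews continue until saturation, so the cells are not hard caps.

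A reader might also infer that the guarantee of 10 per treatment is broken, because SU + RT + ST shows 8. That is not established either. The stated margin for that category is 14. Section 2.10 defines its groups as "treatment(s) received (surgery; chemotherapy/targeted therapy; radiotherapy; no treatment", and even on the printed cells these all reach 10: surgery 68, systemic therapy 60, radiotherapy 34, and no treatment (taken as BSC) 10. The smallest location has 18, above the promised 12. The figure of 8 arises only if the incomplete cells are used and treatment is read as a combination category in Table 1.

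The consequences are softened in other ways. Eight head-and-neck bone patients on systemic therapy are in the printed matrix. The issue list also draws on literature and on interviews with healthcare professionals. Part B plans 12+16 = 28 soft-tissue head-and-neck patients on systemic therapy and asks for missing issues.

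Finally, the Phase 1a block is visibly disturbed: location totals sit on the radiotherapy line, and the cell in question is blank where empty strata elsewhere carry a dash. Typesetting or conversion could have blanked a cell. It is a less likely cause of a whole labelled row disappearing, and Phase 1b reconciles throughout, but it cannot be fully excluded.

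What stands after all this is the contradiction between cells and margins, in the table that decides who is invited.

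**Conclusion.** Wrong as written. The Phase 1a cells sum to 140 against a stated 154. The gap of 14 is 6 localized and 8 metastatic or relapsed places, all for soft-tissue head-and-neck patients on systemic therapy. Head and neck shows 18 against 32, soft tissue 86 against 100, SU + RT + ST 8 against 14, and ST only 52 against 60. The stated targets are coherent and meet the minimum numbers promised, so the error lies in the printed matrix and not in the planned sample size. It matters to the extent that invitations follow the cells and not the margins. The conclusion assumes that the table in the article is as it reads here, and that the margins, which agree with each other and with the text, are the intended figures.

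**What to change.** Check Table 1, Phase 1a, against the source matrix. If the entries are absent there or in the published table, add the localized soft-tissue SU(+RT) + ST row with 6 head-and-neck places, and enter 8 in the head-and-neck cell of the metastatic soft-tissue ST row. Cells and margins then agree at 154. Return the location totals to the per-location line. Keep the stated totals and the guarantee of 10 per treatment; restating the total as 140 would alter a consistent set of targets to fit an incomplete table.

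Section 2.1 says recruitment began in May 2019, so the coordinator should also confirm which version of the matrix has been in use, count how many of the 14 places have been filled, and notify sites. The cost is one table correction and one notice, with no patients beyond the stated 154.

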### 2.10. Statistical Analysis

We will perform thematic analysis of the qualitative data. Transcripts of the patient and HCP interviews will be examined by two coders in detail in order to identify basic patterns and recurrent themes using line-by-line coding to examine, compare and begin to develop conceptual categories. Categories will be developed inductively using the constant comparison method. Comparing each item with the rest of the data to create analytical categories, and then grouping categories together will make it possible to identify key themes [50]. The consolidated criteria for reporting qualitative research (COREQ) will be followed to ensure the accuracy of this qualitative study [51].

Data from patient and HCP interviews and questionnaires will be analyzed according to the EORTC module development guidelines [36], using basic quantitative analyses, including descriptive statistics (e.g., missing data, means and standard deviations, floor and ceiling effects), prevalence (number of patients who experienced each complaint, i.e., who scored 2, 3 or 4, divided by the total number of patients who completed that item, multiplied by 100), priority ratings (number of patients and professionals who have given priority ratings to each item) and range of responses for each item.

In order to facilitate transparent decision-making concerning the best approach to take in developing a sarcoma measurement strategy, the existing decision criteria will be followed: (1) an inclusive approach will be taken with regard to relevant items; (2) inclusion of an issue will be considered when more than 30% of patients (in total or per subgroup) mention the issue as missing; (3) issues that have a low (e.g., mean <1.5) mean score for relevance or importance will be considered for exclusion.

To distinguish “sarcoma generic” from “subgroup-specific issues”, issues that are more or less frequent in specific subgroups will be evaluated. An issue will be coded as endorsed by a respondent if it was scored 2 (“a little relevant”) or higher on the 4-point response scale. An issue needs to be endorsed by at least 30% of the patients in a subgroup to be included as an issue in that subgroup. If an issue is endorsed by patients from 3 out of 6 tumor locations and 2 out of 4 treatment groups, it will be considered to be a generic sarcoma issue; otherwise, it can be considered a sarcoma subgroup-specific issue.

Additional analyses will be performed per subgroup for location, treatment(s) received (surgery; chemotherapy/targeted therapy; radiotherapy; no treatment), type of sarcoma (soft tissue vs. bone sarcoma), and disease stage (localized vs. metastatic). An issue needs to be endorsed by at least 30% of the patients in a subgroup, and the mean score needs to be 1.5 or higher to be included as an issue in a subgroup. Then the prevalence of each issue between the aforementioned subgroups (according to location, type of treatment, subtype and disease stage and combinations of these factors) will be compared to decide whether an issue is subgroup-specific. Issues that are cited by at least 1.5 times as many respondents in group A compared to group B (a ratio of 3:2) may be considered as subgroup-specific.

For head and neck, and uterine sarcoma patients, the scores on the H&N43 and EN24 will be analyzed. We will assess the prevalence (percentage of the subjects who score higher than 2 is >30% and a mean score of 1.5 or higher) of each site-specific item. When at least 80% of the items are prevalent, using the site-specific module for those sarcoma locations will be recommended.

All the collected information will help to advise researchers as to which factors need to be taken into account when creating an item list for a specific study focusing on subgroups of sarcoma patients.

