Usually, the development of a tumor-specific module resolves the problem of insufficient content coverage of a generic measure. A comprehensive sarcoma-specific HRQoL measure for use in clinical trials is currently lacking, as existing HRQoL measures for sarcoma patients are focused on physical functioning only (e.g., Toronto extremity salvage score (TESS) as a measure of physical disability [30]) or patient experiences (e.g., sarcoma assessment measure (SAM) [31]). However, it was found during the development process of the SAM that tumor location and type of treatment received are important factors that determine which HRQoL issues subgroups of sarcoma patients are dealing with, in addition to established factors including sex and age [32,33]. For example, five issues (not specified) were identified to be only relevant in patients who had undergone amputation, and nine issues were relevant to head and neck sarcoma patients [31]. This heterogeneity of the disease was also reflected in HRQoL outcomes in German sarcoma patients and survivors [34]. These data show that the development of a single instrument is challenging, and it may not be the best option to meet the needs of academia and industry to assess the impact of new treatments [15,35].

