### 2.5. Recruitment

Patients will be recruited from Northern Europe (e.g., Germany, The Netherlands, Norway), Central/Eastern Europe (e.g., Poland), Southern Europe (e.g., Cyprus, France, Italy, Spain), the United Kingdom and also in countries outside Europe, including Australia, Canada, Hong Kong, India, Israel, Jordan, and the United States.

The study coordinator will use stratification to ensure that subjects represent the target population and will communicate to the local collaborators which patients can be invited. Purposive sampling will aim to achieve good representation according to sex, age, sarcoma location and treatment. When selecting the patients for interviews, care will be taken to include both younger and older patients, males and females, all types of treatment, as well as newly diagnosed patients and patients in posttreatment follow-up. We will stratify our sample according to the 6 locations of sarcoma (upper and lower extremities, axial skeleton, retroperitoneal/intra-abdominal, head and neck including the scalp, thorax including breast, and pelvic organs including urogenital), disease stage (localized, metastatic disease/local relapse) and subtype (bone sarcoma, soft tissue sarcoma) to ensure the heterogeneity of sarcomas in terms of subtypes, treatments, age, sex, and physical impairments is adequately covered (Table 1). These characteristics are based on the clinical experience of health care professionals and researchers in the sarcoma field and input from patient representatives.

During part A, eligible patients will be identified from the Medical Oncology, Radiation Oncology or Surgery departments of the participating hospitals and through patient organizations. The health care professional will introduce the study to eligible patients. If a patient expresses interest, he or she will be approached by the researcher for further details about the study, the interview, and the agreement to participate.

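### No subgroup factor identifies amputation or separates arm from leg, so issues specific to these patients may be diluted below the 30% bar or assigned to too broad a group

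*Protocol article*

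**What the plan says.** The Introduction argues that tumor location and type of treatment shape which issues a patient faces. Its examples are nine issues relevant to head and neck patients and five that "were identified to be only relevant in patients who had undergone amputation". Section 2.8 makes the primary objective a strategy that says which issues to ask of everyone and which only of certain subgroups.

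The subgroups are fixed elsewhere. Section 2.5 stratifies by "6 locations of sarcoma (upper and lower extremities, axial skeleton, retroperitoneal/intra-abdominal, head and neck including the scalp" and two further sites, so both limbs count as one location; Table 1 accordingly has a single extremities column. Section 2.10 lists four treatment levels: surgery, drug treatment, radiotherapy and none. Prevalence is compared "according to location, type of treatment, subtype and disease stage and combinations of these factors".

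The rules in Section 2.10 are:

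- Endorsement: "An issue will be coded as endorsed by a respondent if it was scored 2 (“a little relevant”) or higher".
- Inclusion in a given subgroup: "An issue needs to be endorsed by at least 30% of the patients in a subgroup". For the additional subgroup analyses, "the mean score needs to be 1.5 or higher to be included as an issue in a subgroup" is also required.
- Specificity: an issue may be called subgroup-specific if its prevalence in one group is at least 1.5 times that in another (3:2).

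**The concern.** The factors that decide where an issue is assigned are coarser than the evidence used to justify them. Head and neck, the other example in the Introduction, has its own stratum and module; amputation has neither. Crossing location, treatment, subtype and stage in any way leaves amputation mixed with limb-sparing surgery, and arm mixed with leg.

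At stake is the main product of the study, the list of what to ask whom, for its largest location (210 of 475 patients in part B). An amputation-only or arm-only issue may fail the prevalence bar because most of the group does not have the problem. If it passes, it is attached to the whole group and asked of patients to whom it does not apply. Likewise, a walking issue that passes is attached to patients with arm sarcomas.

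**Working it through.** **Inputs from Table 1, phase 1b.** Extremities column: 20+20+20+10+40 (localized, all surgical) + 20+30+10+30 (metastatic or relapse) + 10 (best supportive care) = 210, as stated. All six columns: 210+40+65+40+80+40 = 475, as stated. Surgery: 99+96+40 = 235, as stated.

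**Endorsers needed at 30%.**

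| Group | n | Needed |
|---|---|---|
| All extremity | 210 | 0.30 × 210 = 63 |
| All surgery | 235 | 0.30 × 235 = 70.5, so 71 |
| Localized extremity surgery | 20+20+20+10+40 = 110 | 33 |
| Localized extremity bone surgery | 20+20+20 = 60 | 18 |

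**Dilution.** Let a be the amputee share of a group, e the endorsement among amputees and b that among the rest. Pooled prevalence = a·e + (1−a)·b, so the share needed is a = (0.30−b)/(e−b). The article gives none of these quantities; the values below are assumptions.

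| e | b | Share needed |
|---|---|---|
| 100% | 0 | 30% |
| 80% | 0 | 37.5% |
| 50% | 0 | 60% |
| 100% | 10% | 0.20/0.90 = 22% |
| 100% | 20% | 0.10/0.80 = 12.5% |

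With e = 100% and b = 0, amputee shares of 10%, 20%, 30% and 40% give pooled prevalences of 10%, 20%, 30% and 40%. If all 63 endorsers in the extremity group came from its 110 localized surgical patients, 63/110 = 57% of these would have to be amputees. Adding the 20+10 = 30 local-treatment patients in the metastatic or relapse rows lowers this to 63/140 = 45%.

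**Mean rule.** If amputees score m on average and everyone else scores 1, the group mean is 1 + a(m−1). Reaching 1.5 needs a ≥ 0.5/(m−1): 50% for m = 2, 25% for m = 3 and 16.7% for m = 4. The mean rule is stricter than the 30% rule only when amputees score low.

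**Limb.** With no endorsement from the other limb, the endorsement needed is 0.30 divided by that limb's share of extremity patients (the share is also an assumption):

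- Arm share 20%: 150%, which is impossible. 30%: 100%. 40%: 75%. 50%: 60%.
- Leg share 50%: 60%. 80%: 37.5%.

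Leg issues can therefore pass readily, while arm issues may not.

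**If the issue passes.** At exactly 63 of 210, the other 147 (70%) would be assigned an issue that they did not endorse; at 18 of 60, the other 42 (70%).

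**With amputation as its own level.** Prevalence in that level is simply e, so the issue qualifies on the 30% rule whenever e ≥ 30%, whatever the amputee share. The 3:2 rule then compares e with b directly.

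**The case against.** A reader might infer that amputation-specific issues cannot reach 30% and would be discarded. The document does not support this, for three reasons.

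- The 30% rule decides whether an issue is included in a given subgroup. Nothing in Section 2.10 deletes an issue from the list for missing it. Removal is a separate step, only considered when the mean is low, and under a stated inclusive approach. The literature search and open interviews can still bring such issues onto the list.
- Whether the bar is reached depends on an amputee share that the article does not give. Combinations of factors include the 60-patient bone surgery group, where 18 amputees would suffice, and smaller cells such as the 20 extremity bone patients with surgery alone, where 6 would. Because a score of 2 counts as endorsement, some non-amputees may endorse as well.
- The same holds for the arm: at an assumed share of 35% and full endorsement, an arm-only issue passes.

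It can also be said that the Introduction uses amputation to argue against a single instrument, without promising an amputee subgroup; that the strata rest on clinical experience and patient input; and that the full data form, which is not shown, may already hold both items.

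All of this stands against a claim of certain loss. It does not answer the narrower point. The location and treatment levels are written out, and an issue that passes in an enriched cell is still labelled by bone subtype or surgery, never by amputation or limb.

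**Conclusion.** The point holds in its limited form. Without any assumption about rates, the listed factors cannot yield a recommendation addressed to amputees, or to arm or leg patients, although the Introduction presents amputation as a treatment that determines which issues matter.

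Whether an issue is also lost from a subgroup is conditional. With endorsement by all amputees and no one else, it falls short wherever amputees are below 30% of the group. The required share rises if fewer amputees endorse and falls if others do. The amputee and limb shares are unknown, so no probability of loss can be given. This is an inexpensive improvement to the subgroup definitions; it does not invalidate the design.

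**What to change.** 1. Ensure that the clinical data form records, for extremity sarcoma, upper or lower limb and amputation or limb-sparing surgery. Section 2.6 already has clinical data taken from the medical file, so the same source serves, including for patients already enrolled.
2. In Section 2.10, add both as subgroup factors within extremities. Apply the existing 30%, mean 1.5 and 3:2 rules to them descriptively, and report the number of patients beside each percentage.
3. Use the purposive sampling of Section 2.5 to include both levels of each factor within the existing extremity quotas (42 in phase 1a, 210 in phase 1b).
4. Where a new subgroup has fewer than 10 patients, the minimum per location and per treatment that Section 2.9 sets for part B, report the result as indicative only.

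The cost is two data items and two further tabulations, with no added patients. The drawback is imprecision: in a group of 10, one patient moves the percentage by 10 points and 3 endorsers meet the bar.

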**Total**							
Per location	210	40	65	40	80	40	475
Per treatment							
SU only:							99
SU + RT:							96
SU + RT + ST:							40
Surgery total:							235
RT total:							136
ST only:							172
ST total:							212
Local:							38
Per subtype							
Bone:							175
Soft tissue:							300

^a^ Covered by axial group; SU = surgery; ST = systemic therapy (e.g., chemotherapy, tyrosine kinase inhibitors, immunotherapy); RT = radiotherapy; BSC = best supportive care; local treatment = SU and/or RT in metastatic setting.

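### Section 2.10 labels a non-generic issue subgroup-specific without comparing groups, and does not reconcile this with the 1.5-fold contrast in Sections 2.8 and 2.10

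*Protocol article*

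**What the plan says.** The fourth paragraph of Section 2.10 sets the sorting rule. A respondent endorses an issue with a score of 2 or more on the 4-point scale. Inclusion is then decided group by group: "An issue needs to be endorsed by at least 30% of the patients in a subgroup to be included as an issue in that subgroup". The generic rule follows: "If an issue is endorsed by patients from 3 out of 6 tumor locations and 2 out of 4 treatment groups", the issue is generic; "otherwise, it can be considered a sarcoma subgroup-specific issue".

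The fifth paragraph, introduced as additional analyses, adds a subgroup mean of at least 1.5 to the inclusion criteria. It says that prevalence will be compared between subgroups to decide on specificity, and that an issue cited by at least 1.5 times as many respondents in a group A as in a group B may be considered specific. Section 2.8, secondary endpoint 5, names the same 1.5-fold contrast.

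Neither place says whether the contrast overrides, qualifies or merely supplements the *otherwise* clause, or who makes up group B. Section 2.9 and Table 1 give the Part B sizes: 475 patients, with locations of 210, 40, 65, 40, 80 and 40.

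**The concern.** Failing a count of groups is not evidence that groups differ. An issue of equal relevance everywhere, somewhat below 30%, can cross the bar by chance in one or two small groups. It then fails the generic rule and can be called specific to those groups. The bar is applied to point estimates, so crossings fall mostly on the smaller locations.

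Separating sarcoma-generic from subgroup-specific issues is the primary objective in Section 2.8. A false label would lead trialists to ask about an issue only in, say, axial or pelvic sarcoma when its relevance is the same elsewhere. Two analysts could also follow different sentences of Section 2.10 and reach different lists from the same data.

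**Working it through.** **Inputs.** The phase 1b cells of Table 1 sum to 210 + 40 + 65 + 40 + 80 + 40 = 475, which reproduces the stated total. Treatment groups from the same table are surgery 99 + 96 + 40 = 235, systemic therapy 172 + 40 = 212, radiotherapy 96 + 40 = 136, and best supportive care 30, taken here as the no-treatment group (an assumption). The treatment groups overlap. The protocol gives no expected endorsement, so a true value p, equal in every group, is assumed and varied.

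**Step 1: chance that one group reaches the bar.** P(X ≥ k), with X binomial(n, p) and k the smallest whole number at or above 0.3n. At p = 25%:

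| Group size n | k | Chance |
|---|---|---|
| 40 (three locations) | 12 | 28.5% |
| 65 | 20 | 17.5% |
| 80 | 24 | 18.2% |
| 210 (extremities) | 63 | 5.8% |
| 30 (supportive care) | 9 | 32.6% |
| 136 | 41 | 10.1% |
| 212 | 64 | 5.0% |
| 235 | 71 | 4.0% |

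At least one location: 1 − 0.942 × 0.715³ × 0.825 × 0.818 = 76.7%.

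**Step 2: the *otherwise* clause alone.** Simulation on the Table 1 cells keeps the overlap between treatment groups. An issue counts as labelled if at least one of the ten groups reaches 30% and the generic rule fails.

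| True endorsement in every group | Labelled subgroup-specific |
|---|---|
| 10% | 0.3% |
| 15% | 6% |
| 20% | 36% |
| 25% | 81% |
| 28% | 71% |
| 30% | 43% |
| 35% | 2% |

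At 25% the generic rule is met in only about 3% of studies. Three ways of forming the treatment groups give 80.5% to 80.8%. For locations only, 76.7% less the roughly 3% that are generic gives the simulated 74%.

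**Step 3: adding the protocol's own ratio, at 25%, for location labels.**

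| Rule | False location labels |
|---|---|
| *Otherwise* clause alone | 74% |
| plus ratio ≥ 1.5 against any other location | 63%; 66% if exact ties at 1.5 count |
| plus ratio ≥ 1.5 against all other patients | 19% |
| plus 95% CI of that ratio above 1 | 15% |

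Ties matter because 12/40 against 8/40 is exactly 1.5. The CI uses ln(ratio) ± 1.96 × √(1/a − 1/n + 1/b − 1/(475 − n)), where a and b are the endorsers inside and outside the group. Over locations and treatment groups together, the ratio leaves about 71% (any pair) or 26% (all others) of the 80.5%.

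**Step 4: the mean condition.** Requiring a subgroup mean of at least 1.5, without the ratio, leaves 56% at 25% if endorsers split 60/30/10 over scores 2, 3 and 4, and about 80% if their scores are evenly spread or high. These splits are assumptions.

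**Step 5: detection of a truly specific issue.** For a 40-patient location at 50%, 45% or 40% against 15% elsewhere, the present clause detects 99.7%, 98% and 93%. With the ratio against all others and the CI, the figures are 99.6%, 98.1% and 92.6%.

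**The case against.** The plan is not without a contrast. The fourth paragraph of 2.10 opens by saying that differences in frequency between subgroups will be evaluated, the fifth says that a comparison will decide specificity, and endpoint 5 repeats the 1.5-fold threshold. The *otherwise* sentence is permissive and can be read as a screen. On that reading the 81% belongs to one clause, not to the final label. This stands: a reader who takes the plan to have no comparison at all, or about 80% of evenly spread issues to end up falsely labelled, goes beyond the documents.

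It also stands that 25% is assumed and lies close to the peak, and that the existing ratio against all other patients does most of the corrective work (74% to 19%), with the interval adding about 4 points. The minimum in Section 2.9, "at least 10 patients per location and 10 per treatment will be recruited", should not be read as the size of the groups at issue: every location or treatment group used here has at least 30. Finally, this is a descriptive first-phase study with a declared inclusive approach, so an extra issue in one subgroup is a modest harm.

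What the objection does not settle is which rule governs. The ratio sits under additional analyses in equally permissive wording and is nowhere a condition of the label. If any group may serve as comparator, it removes few false labels.

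**Conclusion.** The point holds as an unreconciled definition of subgroup-specific with an undefined comparator. Its effect is large for issues near the 30% bar and small elsewhere: the clause alone gives 6% at 15% endorsement, 81% at 25% and 2% at 35%. At 25%, the open choice of comparator moves false location labels between 19% and 63% to 66%.

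These figures assume equal true endorsement in all groups, recruitment exactly as in Table 1, and best supportive care as the no-treatment group. They use the milder reading in which a labelled issue must reach 30% somewhere; read literally, *otherwise* would also cover issues that reach it nowhere. The documents do not show how many listed issues will lie near the bar, so no overall share of false labels can be stated. The change is worth making because it concerns the rule that delivers the primary objective.

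**What to change.** Replace the *otherwise* clause in Section 2.10 with wording such as: An issue that is not generic is subgroup-specific only if, in that subgroup, endorsement is at least 30%, the mean score is at least 1.5, and prevalence is at least 1.5 times that in all other patients. Any other non-generic issue is listed as a low-prevalence issue without a subgroup label.

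Name the same comparator in endpoint 5 of Section 2.8 and in the fifth paragraph of 2.10. Report each subgroup prevalence and ratio with its 95% CI. Requiring the CI to lie above 1 is an optional refinement, worth about 4 points at 25% (19% to 15%).

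The cost is a few sentences and routine interval output, with no extra patients or data. The downside is a third, unlabelled class and a somewhat shorter list of subgroup-specific issues. In the scenarios of Step 5, detection of a truly specific issue in a 40-patient location is almost unchanged.
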